**Fig. 3 Fig3:**
[figure not shown]
Methods

#### Step 1: Survey of all UFMG directors and the professionals working in the UFMGs

##### Data sources

Three data sources will be used:
The **Minister of Health and Social Services (MHSS) data bank on UFMGs**, which includes a range of data, in particular the number of patients registered and the number and types of different professionals.An **organizational survey** of the 47 directors of all UFMGs.**Providers’ survey** covering three types of professionals working in the UFMGs.

##### Measurement instruments

The *implementation of advanced access* will be assessed in both the organizational and provider surveys by measuring each of the five guiding principles of advanced access [35, 36] including their different sub-dimensions using a 5-point Likert scale. This section of the questionnaires is based on the work of: 1) VanDeusen et al. [10], who developed a questionnaire reflecting the operationalization of certain sub-dimensions of the guiding principles, as well as on a practice guide, *Advanced Access and Efficiency Workbook for Primary Care*, developed by *Health Quality Ontario* [37], which presents the operational definitions of the guiding principles of advanced access and 2) Orchard, King, Khalili et Bezzina [38] who designed and validated a short version questionnaire entitled *Assessment of Interprofessional Team Collaboration Scale*, particularly eight items on partnership. The *MIDI-Measurement Instrument for Determinants of Innovation*, developed by Fleuren et al. [31] will be used in both surveys to assess the *factors influencing the implementation of advanced access* in the UFMGs. The version of UFMG directors also includes an organizational survey based on the work of the Canadian Institute for Health Information [39], whose approval is already obtained. Some questions were, however, removed given that they were considered less relevant for this study or when the information was already available in the MHSS data bank. A pretest was done in the spring 2019 within a pilot project conducted in three UFMGs in one region (Estrie). Funded by the *Fondation Vitae*, this pilot project had enabled us to test the questionnaires in a real-world context and to improve them for the present study.

##### Participant recruitment

All UFMGs (*n* = 47) in the province will be invited to participate. To encourage their participation, we will adopt a personalized approach via one of the four practice-based research networks on primary care (PBRNs). We will request the support of the directors of the departments of medicine and emergency medicine of Quebec’s four faculties of medicine, along with four physician members of our team involved in each of the PBRNs. The 47 UFMG directors will be invited by email to respond to the organizational survey which will be developed in a digital format using the *Survey Monkey* platform. Based on the pilot survey, we are confident we will be able to achieve a response rate of about 80% from the UFMG directors (organizational survey), given the close partnerships already established with clinical leaders involved in this project, as well as the previous experience of our research team members who have conducted projects in UFMGs that generated high satisfactory response rates.

With respect to the questionnaires for professionals, all physicians, residents, nurse clinicians, and primary care nurse practitioners working in the UFMGs will be invited by email to participate in the study. Working in close partnership with the PBRNs, this study will be promoted, and the invitations will be sent by UFMGs key collaborators (e.g. manager, physician in charge or head of research, continuous quality improvement officer).

Three reminder emails will be set-up and sent at regular intervals, i.e., after 1, 2, and 4 weeks, to increase the response rate [40]. Currently, there are approximately 980 physicians, 80 nurse clinicians, and 90 PCNPs working in the UFMGs. To reach a power of at least 94.9%, we estimate that we will need a response rate of 25% for physicians and residents, with a 5% margin of error. To achieve a power of at least 82%, we estimate that we will need a response rate of 40% for the nurses and primary care nurse practitioners.

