##### B) Quantitative component

***Data collection***

Impact analyses will be conducted in the four selected UFMGs. We will use data retrieved from the electronic medical records (EMR) for the three first indicators presented below and data from the MHSS data bank for the fourth indicator. All UFMGs in Quebec have a functional EMR system. Because the UFMGs are attached to health facilities, we will be able to obtain all the EMR data for research purposes with the authorization of the directors of professional and hospital services without needing explicit consent from patients. On average, there are 20 physicians, 18 residents, two nurse clinicians, and one primary care nurse practitioner working in each UFMG, with an average of 5112 patients registered [45]. Thus, we calculated the estimated numbers in our samples as follows: around 160 professionals and 20,000 patients. The four indicators will be measured monthly over a one-year period.

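### The 94.9% and 82% given for the provider survey are not power, and neither matches the group it is attached to under the usual survey-precision formula

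*Protocol article*

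**What the plan says.** All the figures at issue stand in the Protocol article, Step 1, Participant recruitment, except the last.

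- Who is invited: "all physicians, residents, nurse clinicians, and primary care nurse practitioners working in the UFMGs will be invited by email".
- Population counts: "there are approximately 980 physicians, 80 nurse clinicians, and 90 PCNPs working in the UFMGs". No resident count is given there.
- Physicians and residents: "To reach a power of at least 94.9%, we estimate that we will need a response rate of 25% for physicians and residents", followed by "with a 5% margin of error".
- Nurses and PCNPs: "To achieve a power of at least 82%, we estimate that we will need a response rate of 40% for the nurses" and PCNPs. This sentence states no margin.
- Step 2, B) Quantitative component, Data collection, gives averages per clinic: "On average, there are 20 physicians, 18 residents, two nurse clinicians, and one primary care nurse practitioner working in each UFMG".

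The Analysis section of Step 1 plans implementation scores by type of professional, aggregation to clinic (UFMG) level, and linear and logistic regressions of the scores on candidate factors. It does not mention either percentage.

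**The concern.** Power is the probability of rejecting a stated null hypothesis when a stated effect is true. The text gives a response rate and, for one group, a margin of error. Those inputs yield a precision or a confidence level, not a power. A reader may take the two percentages as assurance that the regressions under objective 1 can detect the factors of interest, and nothing in the article supports that.

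The denominator is also unclear. Residents are named in the 25% target but are not counted where the target is set. A 25% response could therefore mean about 245 questionnaires (physicians only) or about 456 (physicians plus residents). The nurse and PCNP groups are small, so their real precision matters for scores reported by type of professional.

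**Working it through.** **Inputs from the Protocol article.** 980 physicians, 80 nurse clinicians and 90 PCNPs; response targets of 25% and 40%; margin of 5% for physicians and residents (Step 1, Participant recruitment). 47 clinics; 20 physicians, 18 residents, two nurse clinicians and one PCNP per clinic on average (Step 2, B, Data collection).

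**Assumptions.** p = 0.5, simple random response within each group, normal approximation, and the ±5% margin carried over to nurses and PCNPs for the comparison only.

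**Derived populations**
- All counted professionals: 980 + 80 + 90 = 1,150.
- Residents: 18 × 47 = 846. Since 20 × 47 = 940 is close to 980, the 980 appears to exclude residents.
- Physicians plus residents: 980 + 846 = 1,826.
- Nurses plus PCNPs: 80 + 90 = 170.

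**Formulas**
- se = √[0.25/n × (N − n)/(N − 1)]
- Confidence at ±5% = 2Φ(0.05/se) − 1
- 95% margin = 1.96 × se

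**Reproducing 94.9%.** N = 1,150, n = 287 (25%): se = √(0.25/287 × 863/1,149) = 0.02558; 0.05/se = 1.955; confidence = 94.94%. This matches to the stated decimal, but the population includes nurses and PCNPs and excludes residents.

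**The groups named**

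| Group | N | n | se | Confidence at ±5% | 95% margin |
|---|---|---|---|---|---|
| Physicians only | 980 | 245 | 0.02768 | 92.9% | ±5.4% |
| Physicians + residents | 1,826 | 456 | 0.02029 | 98.6% | ±4.0% |
| Nurses + PCNPs | 170 | 68 | 0.04711 | 71.2% | ±9.2% |
| Nurse clinicians | 80 | 32 | 0.06890 | 53.2% | ±13.5% |
| PCNPs | 90 | 36 | 0.06491 | 55.9% | ±12.7% |

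**What would give the stated figures.** With required n = n0/(1 + (n0 − 1)/N) and n0 = z² × 0.25/0.05²:
- 94.9% (z = 1.951, n0 = 380.8): 275 of 980 physicians (28%), or 316 of 1,826 physicians plus residents (17.3%).
- 82% (z = 1.341, n0 = 179.8): 88 of 170 nurses plus PCNPs (about 52%). Alternatively, keeping n = 68, a margin of 1.341 × 0.04711 = 6.3%.

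**Sensitivity to p.** At p = 0.3, 245 of 980 physicians gives 95.1%. At p = 0.2, 68 of 170 gives 81.5%.

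**True power is undetermined.** For a one-sample test with n = 245, power is 34.7% at a standardized effect of 0.10 and 95.0% at 0.23. With n = 68 it is 82.3% at 0.35. Without a stated effect, almost any value can be obtained.

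**Base counts.** PCNPs: 90 in Step 1, against 1 × 47 = 47 implied by Step 2. Nurse clinicians: 80 against 2 × 47 = 94. Physicians: 980 against 940.

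**The case against.** Several stronger readings are tempting, and the article does not support them.

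- **That the physician and resident target fails.** It does not for the group as named. With about 846 residents counted, 25% gives 98.6%, above the stated minimum. A shortfall appears only if residents are dropped, and it is then small (92.9%).
- **That the authors must have used 1,150.** No calculation is shown. The match is exact at p = 0.5, but 980 physicians come close at p = 0.3, and a genuine power calculation with an unstated effect could also give 94.9%. The source is an inference.
- **That nurse precision is about half what the text claims.** The sentence on nurses and PCNPs states no margin, so there is no claimed precision to compare with. The 71% depends on carrying ±5% over.
- **That clustering by clinic widens these margins.** All 47 clinics and every professional of the listed types are invited, so no sample of clusters is drawn. Under simple random response, a simulation with 980 physicians in 47 clinics and 245 respondents gave ±5.4% at assumed intraclass correlations of 0.05 and of 0.20, the same as the simple formula. Clustering matters for the regressions, which are a different quantity.
- **That recruitment stops at these targets.** Nothing says so. Three reminders are fixed at 1, 2 and 4 weeks, and the section on potential challenges adds close follow-up and, if representativeness varies, weighted analyses.

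It can also be said that the two sets of counts are approximate and serve different purposes. That is fair for physicians and nurse clinicians. The PCNP counts differ by a factor of nearly two.

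None of this turns the two percentages into power or says what they describe.

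**Conclusion.** The point holds in limited form. The article labels as power two figures for which it gives no hypothesis, effect size or alpha, and it does not tie them to the planned regressions. Under the standard formula (p = 0.5, finite population correction, ±5%), neither named group reproduces its figure: 92.9% or 98.6% against 94.9% for physicians without or with residents, and 71.2% against 82% for nurses and PCNPs. The last comparison rests on a margin that the sentence does not state. The resident total of 846 is itself derived from a per-clinic average.

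This is a misstatement in the text rather than something left to a fuller document. Severity is minor: no analysis, threshold, case selection or stopping rule in the article depends on either figure.

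**What to change.** In Step 1, Participant recruitment:

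1. Delete both power figures. State instead the 95% margin for a proportion at the target response rate, with p = 0.5, simple random response and finite population correction: physicians about ±5.4%; physicians plus residents about ±4.0%; nurses plus PCNPs about ±9.2% (nurse clinicians alone about ±13.5%, PCNPs alone about ±12.7%). Do not apply a cluster design effect to these margins.
2. Give the resident denominator, and say whether the 25% target applies to physicians and residents together or separately.
3. Reconcile the PCNP count (90, against about 47 implied by the Step 2 averages), and update the margins if the count changes.
4. If a power statement is kept, make it for the Step 1 regressions, with the effect size and alpha stated and clustering by clinic taken into account.

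Items 1 to 3 mean rewording one paragraph and checking the counts. Item 4 needs a new calculation only if power is retained. No extra recruitment is required.

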##### Analysis

To respond to *objective 1* (assess the implementation of the five guiding principles of advanced access in the UFMGs), a score will be calculated for each principle, by type of respondent. Implementation scores will be assessed for each advanced access guiding principle by type of professional. Then, scores will be aggregated to produce group scores at the UFMG level for each of the above-mentioned principles. The median or average of all UFMGs’ score will be used as a threshold to determine the implementation categorization (e.g., strong/weak) of the advanced access for each principle. Descriptive analyses in terms of proportions, means, or standard deviations will be generated to determine the implementation scores of each principle and the factors influencing implementation. Multiple linear and logistic regression analyses will be performed using SAS 9.4 to determine the influence of different factors on implementation scores.

The Phase 1 results will be used to produce an implementation profile (e.g., strong/weak) of the UFMGs to guide the selection of the four cases which will be further analyzed in depth in Step 2.

#### Step 2: Multiple contrasted case study based on mixed data

##### **A)** Qualitative component

***Data collection***

We will select four contrasted cases representing implementation profiles (*n* = 2 cases with high score, n = 2 cases with low score) and various geographical contexts and organizational size of UFMG (n = 2 cases in urban areas, n = 2 cases in rural/semi-rural areas). Previous studies have shown that context have a major influence on the types of collaborative practices among professionals [41].

For each UFMG in the study (*n* = 4), we will first perform a documentary analysis (e.g., algorithm of the patient’s path through advanced access, operating rules for team members). Then, a researcher and the research coordinator will conduct and record semi-structured interviews (60 min; at the UMFG) to reach data saturation (*n* = 11 interviews/case: two physicians, two PCNPs, two nurse clinicians, the physician in charge, one manager, two administrative assistants, one continuous quality improvement officer). The professionals will be recruited by email using purposive and snowball sampling strategies addressing first the medical director [42].

In addition, patients’ perceptions are key to the process of adopting the advanced access model and to its successful implementation. In each of the four UFMGs under study, a researcher and the research coordinator will conduct and record a focus group of patients (120 min; at the UFMG) with different characteristics (age, sex, education level, comorbidity) (*n* = 8–10 patients/focus group) [43] to assess patients’ experiences of care in relation to accessibility issues. This type of sample will be useful to represent and describe the internal diversity of the UFMG’s group of patients. Patients will be recruited in each of the selected UFMGs using different strategies: a poster will be displayed in the waiting rooms; the administrative assistants will be informed of the project and encouraged interested patients in research to participate in the study. We will provide them with letters of invitations containing the required information that patients will need if interested to contact the researchers. Lastly, the professionals themselves could provide verbal information on the research project to patients during their visits. These techniques have already been used in our previous project [7, 22] on advanced access and were successful in recruiting and conducting three focus groups in a single UFMG. The patient partners on our advisory team will be involved in the data collection and results interpretation.

***Analysis***

Thematic analysis based on our conceptual framework will be used to analyze the semi-structured interviews and focus groups. The research coordinator will code the interviews with NVivo software using a mixed deductive (conceptual model) and inductive strategy. A summary list of initial codes based on our conceptual model (five guiding principles of advanced access; contextual, organizational, and professional factors; etc.) will serve a priori as a coding grid. It will be modified and enhanced as the analyses progress. Coding will be controlled using a double coding technique conducted by the research coordinator and a researcher. Parallel and independent coding will be done for the first five interviews, after which the results will be compared. This process will be repeated until a consensual list of initial codes is obtained as well as an inter-coder fidelity greater than 90% [44].

##### B) Quantitative component

***Data collection***

Impact analyses will be conducted in the four selected UFMGs. We will use data retrieved from the electronic medical records (EMR) for the three first indicators presented below and data from the MHSS data bank for the fourth indicator. All UFMGs in Quebec have a functional EMR system. Because the UFMGs are attached to health facilities, we will be able to obtain all the EMR data for research purposes with the authorization of the directors of professional and hospital services without needing explicit consent from patients. On average, there are 20 physicians, 18 residents, two nurse clinicians, and one primary care nurse practitioner working in each UFMG, with an average of 5112 patients registered [45]. Thus, we calculated the estimated numbers in our samples as follows: around 160 professionals and 20,000 patients. The four indicators will be measured monthly over a one-year period.
*The average wait for the third available appointment.* This is the most accurate indicator for measuring the impact of advanced access implementation [37, 46]. It is used to assess the time required for an appointment and refers to the number of business days before the third available appointment in a professional’s schedule, for a regular or follow-up appointment [47]. It reflects availability more accurately than using the first or second available appointment, as these could result from a recent cancellation or an unanticipated event [13, 27]. As suggested by several authors, including the *Quality Improvement Guide* [48], Pickin et al. (2004) [27], and Jones et al. (2003) [49], we will calculate, every Tuesday, the median number of days until the third available appointment, and then the monthly average for each professional in the UFMGs [27].*Average rate of missed appointments (no-shows).* An underlying premises of advanced access is that providing a system of timely appointments leads to greater efficiency, with fewer missed (no-show) appointments [37]. Several studies have shown positive impacts on this indicator [50]. No-shows are defined as appointments that are scheduled but not used, excluding those cancelled or changed by the professional, and that are registered by the administrative staff in the EMR. We will calculate on a monthly basis, for each professional, the number of no-shows in relation to the total number of scheduled appointments [51]*.**Relational continuity.* Relational continuity is an important feature of primary care quality [48]. Patients followed by a professional whom they trust generate fewer visits [48]. While new organizational models rely on patients being managed by a team of professionals, advanced access aims first to optimize appointments with the professional to whom the patient is affiliated, depending on the need for the visit and the professional’s availability. Relational continuity is calculated as the number of visits with the physician and other team partner (e.g., nurses, residents) responsible for that patient’s follow-up care divided by the total number of that patient’s visits at the clinic [37*,*^48^]*. T*his indicator can be broken down into two complementary measures: 1) the number of visits the patient had with his/her affiliated physician divided by total number of visits to the UFMG; and 2) the number of visits with other team partner following that patient (e.g., nurses, residents) divided by the total number of visits to the UFMG. Relational continuity with the team will be obtained on a monthly basis for each patient from the sum of these two measures.*Organizational continuity measures*. The aim of advanced access is that patients will consult the primary care clinic to which they are affiliated to satisfy the majority of their needs. Organizational continuity measures the proportion of primary-care medical services patients receive at their UFMG where they are attached. This is measured by the number of consultations at the UFMG divided by the total number of primary care consultations (including visits both to the UFMG and to the emergency room for less urgent cases). Monthly measures of attendance rates of UFMG patients will be obtained from the MHSS, a partner in this study, which holds accurate measurement data of this indicator for all FMGs and UFMGs since January 2016.

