
***Analysis***

Descriptive analyses will be performed for all data, as well as graphic representations of the changes in monthly rates for each indicator aggregated to the level of each of the four selected UFMGs. Given the hierarchical nature of the data (repeated measures nested at the patient [indicator 3] or professional [indicators 1 and 2] level, which in turn are nested within the UFMGs), we will use multilevel analyses. These models will be adjusted to examine the effects of the various factors and of the implementation levels of advanced access on each of the three indicators. This type of model allows us to take into account the correlation between repeated measures for a single individual (patient or professional) over the study period, as well as missing data and patients lost to follow-up [52]. For the 4th indicator, trends will be analyzed using *join point* regression analyses [53]. This technique will be used to compare attendance rates among the 47 UFMGs and detect whether there have been significant changes in the direction or size of the linear trends for the rates over the 12 months of the study.

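### Relational continuity is set as a patient-month ratio that is undefined in most months, and its stated nesting leaves out the affiliated physician

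*Protocol article*

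**What the plan says.** In the protocol article, Step 2, B) Quantitative component, Data collection, relational continuity counts visits with the responsible physician and team partners, "divided by the total number of that patient’s visits at the clinic". It is split into two parts. The first is "the number of visits the patient had with his/her affiliated physician divided by total number of visits to the UFMG"; the second is the same ratio for other team partners. The unit and period are then fixed: "Relational continuity with the team will be obtained on a monthly basis for each patient from the sum of these two measures". The schedule is general: "The four indicators will be measured monthly over a one-year period". No look-back window, minimum number of visits or rule for a zero denominator is given.

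The Analysis paragraph of the same component gives the hierarchy as "repeated measures nested at the patient [indicator 3] or professional [indicators 1 and 2] level, which in turn are nested within the UFMGs". The professional is thus a level for indicators 1 and 2 only. The chosen model is said to allow for the correlation between repeated measures, "as well as missing data and patients lost to follow-up". No distribution or link is named.

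**The concern.** Two stated choices cause the difficulty.

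- **The unit.** A patient who does not attend in a month has no continuity value for that month. Nothing went unobserved, so there is nothing for a missing-at-random argument to work on. The article also says that patients who trust their professional make fewer visits. On that premise, whether a month has a value may itself depend on continuity. Months that do have a value mostly hold one visit, so the ratio is close to a yes/no outcome.
- **The nesting.** The numerator counts visits with the affiliated physician or team, and the article says this depends partly on that professional's availability. Patients of one physician are therefore likely to be correlated. The Analysis paragraph intends to examine various factors, and the conceptual framework includes professional ones. Standard errors for such factors would be too small if the physician level is left out.

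Relational continuity is one of the three indicators to be modelled for objective 3. As written, the analyst would have to discard most patient-months or improvise a rule after seeing the data.

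**Working it through.** **Stated sample, reproduced.** The inputs are "On average, there are 20 physicians, 18 residents, two nurse clinicians, and one primary care nurse practitioner working in each UFMG" and "with an average of 5112 patients registered".
- Professionals: 4 × (20 + 18 + 2 + 1) = 164, against a stated figure of around 160.
- Patients: 4 × 5112 = 20,448, against a stated 20,000.
- Planned patient-months: 20,448 × 12 = 245,376.

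**Undefined and single-visit months.** The visit rate v per patient-year is an assumption. With monthly visits Poisson, λ = v/12:
- P(undefined) = exp(−λ)
- P(one visit | defined) = λ·exp(−λ) / (1 − exp(−λ))
- P(value exactly 0 or 1 | defined) = Σ P(k)[c^k + (1−c)^k] / P(k ≥ 1), summed over k ≥ 1, where c is the chance that a visit is with the team (assumed 0.5 to 0.9)

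| v per year | Undefined | One visit, if defined | Exactly 0 or 1, if defined |
|---|---|---|---|
| 2 | 84.6% | 91.9% | 95.8–98.5% |
| 3 | 77.9% | 88.0% | 93.8–97.8% |
| 4 | 71.7% | 84.3% | 91.7–97.0% |
| 6 | 60.7% | 77.1% | 87.6–95.5% |

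The undefined share falls to one half only at v = 12 × ln 2 = 8.3.

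Two checks on the Poisson assumption:
- Whatever the distribution, the share of months with a visit cannot exceed the mean number of visits per month. At least 1 − 3/12 = 75% are therefore undefined at v = 3, and at least 1 − 4/12 = 67% at v = 4.
- With uneven use (negative binomial, shape 1), the undefined share at v = 2, 3, 4 and 6 is 85.7%, 80.0%, 75.0% and 66.7%. At v = 6, 66.7% of defined months hold one visit and 80.0–92.6% of values are exactly 0 or 1.

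**Physician clustering.** Patients per provider: m = 5112/20 = 255.6 counting physicians only, or 5112/38 = 134.5 counting residents too. The intraclass correlation (ICC) is an assumption. The design effect is 1 + (m − 1) × ICC:

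| ICC | m = 134.5 | m = 255.6 |
|---|---|---|
| 0.02 | 3.7 | 6.1 |
| 0.05 | 7.7 | 13.7 |
| 0.10 | 14.4 | 26.5 |

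Standard errors would be too small by a factor of √3.67 = 1.9 to √26.46 = 5.1.

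A small simulation points the same way. It used 4 clinics, 20 physicians each, 100 patients per physician, one continuous value per patient, and a physician-level factor with no true effect. At ICC 0.02, 0.05 and 0.10, a test that ignored the physician level rejected in 24%, 44% and 56% of runs. A test at physician level rejected in 4% to 5%.

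**The case against.** Several counter-arguments have force.

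- **No Gaussian model is stated.** A reader might infer that a linear model will be fitted to 0/1 data. The article says only that multilevel analyses will be used, and a logistic or binomial model is also multilevel. Link and distribution are details that an article may leave to the full plan. This stands, so misfit of the model is not claimed here. The unit, period, denominator and nesting, however, are stated in the article.
- **Empty months carry no information under any model.** This stands. A visit-level analysis recovers nothing from them and still describes attenders. The data are also not small in number: at v = 3, about 245,376 × 0.221 ≈ 54,000 patient-months are defined. What remains wrong is treating these months as missing data and leaving the target unclear.
- **Weighting is a minor matter.** If most defined months hold one visit, weighting by month or by visit differs little. This stands.
- **Physician clustering need not dominate.** A reader might infer that it does, but no ICC is given. The article names the patient's need as well as availability. Residents may share panels and team partners count in the numerator, so clean nesting in one physician is not assured. The design effect also compares with full independence, whereas patient and UFMG levels are already in the model.
- **The main contrast is not rescued.** A reader might infer that the missing level invalidates the comparison by implementation level. That comparison rests on four UFMGs, and a physician level does not change this.

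**Conclusion.** The point holds for the indicator's unit and the stated nesting. It should be fixed, but it does not undermine the study: this is one of four indicators in a four-case explanatory study, and no confirmatory test is stated for it.

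At an assumed 2 to 6 visits per patient-year, about 85% to 61% of patient-months are undefined and most of the rest are exactly 0 or 1. That most months are undefined holds for any mean rate below 6 visits a year, whatever the distribution, and below about 8.3 under Poisson.

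For professional-level factors, leaving out the affiliated physician corresponds to a design effect of about 4 to 26 at an assumed ICC of 0.02 to 0.10. These figures are a guide to scale, since neither the visit rate nor the ICC is in the article.

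**What to change.** 1. Make the visit the unit, with two outcomes: seen by own physician (yes/no), and seen by own physician or team (yes/no). Equivalently, keep numerator and denominator per patient-month as binomial counts.
2. Fit a logistic multilevel model with random effects for patient and affiliated physician, and calendar month as a covariate. State how patients on shared resident panels are assigned.
3. Plot monthly UFMG proportions as summed numerators over summed denominators. Graphs at UFMG level are already planned; this settles how they are aggregated.
4. Remove the suggestion that months without visits are handled as missing data, and say that the result describes visits made.
5. If UFMG is entered as fixed effects, the UFMG-level implementation score is collinear with them and cannot be entered too. Present implementation level as a descriptive contrast among the four clinics.

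The cost is low, because the same EMR extract serves. The downsides are a larger analysis file and odds ratios instead of mean differences.
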